# SYNOPSIS

| Trial Title | The efficacy of rupatadine in treating dengue: a randomised, double blinded, placebo controlled trial | |
| --- | --- | --- |
| Short title | Efficacy of rupatadine in dengue | |
| Clinical Phase | Phase 2 | |
| Trial Design | Randomised, double blinded, placebo controlled | |
| Trial Participants | Patients with dengue infection | |
| Planned Sample Size | 280 with 140 each in each study arm | |
| Treatment duration | 5 days | |
| Follow up duration | 30 days of illness | |
| Planned Trial Period | 1 year | |
|  | Objectives | Outcome Measures |
| Primary | To determine the proportions of dengue patients who develop DHF when treated with and without rupatadine | Therefore, the reduction of the proportion of individuals who develop fluid leakage (DHF) will be assessed.  Evidence of plasma leakage: evidence of plasma leakage considered as detection of free fluid in the abdomen or by the presence of a pleural effusion by USScan and/or by the presence of a rise in haematocrit of >20% of the baseline. |
| Secondary | Investigate whether rupatadine treatment leads to a. reduction in complications such as liver failure.  b. Reduction in development of shock:  c. Need of colloids:  d. Need of blood transfusion/s:  e. Duration of the illness.  f. Sleep disturbance | Liver function tests, blood clotting, colloid infusion volumes, blood transfusion volumes, length of acute illness, sleep scores. |
| Investigational Medicinal Product(s) | Rupatadine 40mg | |
| Formulation, Dose, Route of Administration | Four 10mg tablets of rupatadine to be given orally, and placebo | |

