## 8.4 Randomisation, blinding and code-breaking

The randomization schedule will be designed by the statistician and she will be responsible for providing the randomization codes. The tablets of the placebo and the rupatadine will be packed into envelops, which is to be given to each patient. Each envelop will contain tablets needed for the whole duration of treatment (5 days). Once the codes are provided, the packaging will be by individuals who are not involved in the study. The packed and sealed envelopes will be stored at the Centre for Dengue Research and released in small batches to be given to patients. A person who is not involved in the study will be responsible for dispersing these envelops. Therefore, all investigators and the patients will be blinded.

Once the patients are enrolled to the study a serial number is assigned in a chronological order for data entering purposes. Total number of patients will be 262 and all will be treated according to the current Dengue guidelines published by the Ministry of Health, Sri Lanka. The study groups will receive 40 mg of rupatadine in addition to the treatment guidelines (please see below). The two treatments would be named A (40mg rupatadine) and B (placebo). The patients will receive either 4 tablets of rupatadine daily for 5 days or 4 tablets of the placebo for 5 days, which will be prepacked in an envelope containing the code number. This code number will be entered in the data collection sheet along with the patient’s serial number.

Randomization will be done by using a random number table (1-10). Using this table an arbitrary point would be chosen, and the patient would be allocated according to the random number. If the number selected from the random table is between 1 to 5, the patient would be assigned to the treatment arm A. If the number selected from the Random table is between 6 to 10. The assignment information will be kept under lock and key. Neither data collectors nor the patients will be made aware of the randomization at any given point of time.

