## The Number of Participants

This is planned to evaluate rupatidine drug compared to a placebo in reducing the proportion of patients who develop vascular leak (DHF). The response rate of the active control drug, rupatidine in reduction of fluid leakage by Ultra sound scan was found to be 42.8% (p1) and in the standard treatment was 23.5% (p2). The number of participants per group required to detect a difference in the two groups with a significance level of 5% and a power of 1 - β is 280.

[figure not shown]

Given an anticipated dropout rate of 10% , the sample size needed per group is 280.

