# QUALITY ASSURANCE PROCEDURES

The trial will be conducted in accordance with the current approved protocol, GCP, relevant regulations and standard operating procedures.

Regular monitoring will be performed according to GCP. Data will be evaluated for compliance with the protocol and accuracy in relation to source documents. Following written standard operating procedures, the monitors will verify that the clinical trial is conducted and data are generated, documented and reported in compliance with the protocol, GCP and the applicable regulatory requirements.

The DSMB will meet once the trial has recruited half of the participants. The DSMB comprises of a physician, a clinical pharmacologist, a statistician, a general practitioner and a patient who is medically qualified.

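### The planned sample size is stated inconsistently: 280 per group, 280 in total and 262 in total, with 280 per group unchanged by the 10% dropout allowance

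*Protocol*

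**What the plan says.** Three parts of the protocol give a planned size.

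- **Statistics, The Number of Participants.** The number required per group at 5% significance and "a power of 1 - β is 280". After a figure that is not shown, the section continues that, with 10% dropout anticipated, "the sample size needed per group is 280". Both sentences refer to each group, which implies 560 patients.
- **Synopsis, Planned Sample Size.** "280 with 140 each in each study arm".
- **Section 8.4, Randomisation, blinding and code-breaking.** "Total number of patients will be 262", which is 131 per arm under equal allocation.

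The rates behind the calculation are 42.8% and 23.5%. The Number of Participants attaches the first to rupatadine ("in reduction of fluid leakage by Ultra sound scan was found to be 42.8% (p1") and the second to standard treatment. Table 2 in Background and Rationale shows the reverse: ascites in 9 of 21 patients (42.8%) on placebo and 4 of 17 (23.5%) on rupatadine.

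The interim analysis (Description of Statistical Methods) is set at half of recruitment. So is the DSMB meeting: "The DSMB will meet once the trial has recruited half of the participants". Neither section gives a count.

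**The concern.** The section that justifies the size disagrees with the Synopsis by a factor of two and with itself on dropout. A requirement of 280 per group cannot still be 280 per group once 10% are expected to be lost. Section 8.4, which governs allocation and the packing of coded envelopes, adds a third figure that reading 'per group' as 'in total' does not explain.

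The size fixes the enrolment target, the number of envelopes, the number of patients exposed and any statement of power. It also places the interim look, at which Criteria for the Termination of the Trial allows the study to be halted or modified on the DHF result. If 560 were the plan, that look would come at 280 patients, which is where the Synopsis has enrolment complete.

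**Working it through.** **Inputs.** p1 = 0.428, p2 = 0.235 and 10% dropout (The Number of Participants); significance level 0.05 (The Level of Statistical Significance); equal arms (Synopsis). Assumed: a two-sided test, because sidedness is not stated, and a power range of 80% to 99%, because the readable text gives power only as a symbol and the missing figure may hold the value.

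**Step 1: internal check on dropout.** If 280 per group is the need before dropout, recruitment is 280/0.9 = 311.1, so 312 per group (624 in total). If 280 per group is the number to recruit, the need before dropout is 280 × 0.9 = 252. The section gives 280 for both.

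**Step 2: can 280 per group be reproduced?** With p̄ = 0.3315 and difference 0.193:

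n = [z(α/2)·√(2p̄(1−p̄)) + z(β)·√(p1(1−p1)+p2(1−p2))]² / (p1−p2)²

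Here 2p̄(1−p̄) = 0.4432, p1(1−p1)+p2(1−p2) = 0.4246 and (p1−p2)² = 0.03725. At 90% power:

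n = (1.960 × 0.6657 + 1.282 × 0.6516)² / 0.03725 = 122.9, so 123.

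| Power | n per group | after ÷0.9 |
|---|---|---|
| 80% | 93 | 104 |
| 90% | 123 | 137 |
| 95% | 152 | 169 |
| 99% | 214 | 238 |

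One-sided tests, a continuity correction and other variance forms were also tried, up to 99% power. The largest result was 224 per group before dropout and 249 after (99%, two-sided, continuity-corrected). None reaches 280 per group.

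**Step 3: can 280 in total be reproduced?** With the pooled variance used throughout, at 90% power:

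n = (1.960 + 1.282)² × 0.4432 / 0.03725 = 125.02, rounded up to 126.

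Then 126/0.9 = 140 per group, or 280 in total. The formula in Step 2 gives 137 per group, or 274. So the Synopsis figure follows from the protocol's rates at an assumed 90% power. The route is not unique: a one-sided 5% test at 95% power gives 127 per group, and 127 × 1.1 = 139.7 also rounds to 140.

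**Step 4: can 262 be reproduced?** Only approximately. The unpooled form at 90% power gives 119.8, so 120 per group, and 120 × 1.1 = 132, or 264 in total. Cutting 119.8 down to 119 gives 119 × 1.1 = 130.9, so 131 per group, or 262. The protocol shows no such route, so this is conjecture.

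**Step 5: power at each stated size,** from Φ{[√n × 0.193 − 1.960 × 0.6657] / 0.6516}:

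| Stated size | Per arm | Power, all evaluable | Evaluable after 10% loss | Power |
|---|---|---|---|---|
| 262 in total | 131 | 91.7% | 118 | 88.8% |
| 280 in total | 140 | 93.3% | 126 | 90.7% |
| 280 per group | 280 | 99.8% | 252 | 99.7% |

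**Step 6: the halfway point.** 560/2 = 280; 280/2 = 140; 262/2 = 131.

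**The case against.** The strongest reply is that 'per group' in The Number of Participants is a slip for the total. The Synopsis is unambiguous, gives the split by arm and agrees with the protocol's own rates at 90% power. This stands as the most likely explanation. It does not explain 262, and it does not explain why the number before dropout is also 280.

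Three stronger readings are tempting, and the document does not support them.

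- A reader might infer that the trial's size and interim point are undefined. The Synopsis does define a coherent size. Setting an interim look at half of recruitment is ordinary practice, and the count follows once the size is settled.
- A reader might infer that no power was specified. The figure missing from The Number of Participants directly follows the sentence with the power symbol and may contain the value, so its absence cannot be held against the plan.
- A reader might infer that the trial could be badly underpowered. The factor of two arises only if 'per group' is taken literally. Between 262 and 280 the gap is 18 patients, or about two percentage points of power (88.8% against 90.7% after dropout).

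**Conclusion.** The point holds as an inconsistency in a figure on which the trial relies. The protocol implies totals of 560, 280 and 262, and its dropout step leaves the per-group number unchanged, which is arithmetically impossible. Its own rates support about 280 in total: 123 to 126 per group at 90% power, 137 to 140 after dropout. At 280 per group the power would be about 99.8%, which no usual planning target explains.

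The dropout contradiction and the conflict between sections need no assumption about power or sidedness. The judgement that about 280 in total is what the rates support assumes a two-sided 5% test and 90% power. It also takes the two rates as given. They are ascites rates from 21 and 17 patients, whereas the primary endpoint also counts pleural effusion and a haematocrit rise above 20%, so the power figures show which size matches the stated calculation and do not validate the rates. The reversal of the arms against Table 2 does not change the required number.

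**What to change.** Use one size in the Synopsis, section 8.4 and The Number of Participants. In the last, give the number before dropout and the number to recruit separately, state the power delivered, and label the rates by arm as in Table 2.

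If the Synopsis figure is kept, the text could read: *140 per group, 280 in total; 126 evaluable per group after 10% dropout gives about 90.7% power at two-sided 5% to detect 42.8% on placebo vs 23.5% on rupatadine.* Section 8.4 would then say 280, and the interim analysis and DSMB meeting would be set at 140 patients recruited.

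If another size was intended, the same places need the matching numbers: its power after dropout and half its total as the interim count.

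The cost is corrected text in these sections. Keeping the Synopsis figure adds no patients to the planned 280.

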## The Level of Statistical Significance

The level of significance will be 0.05.

## Criteria for the Termination of the Trial

In the light of interim data the DSMC will inform the PI, if, in their view, there is proof beyond reasonable doubt that the data indicate that the trial should be terminated. A decision to inform the PI of such a finding will in part be based on statistical considerations and side effects. Appropriate proof beyond reasonable doubt cannot be specified precisely. A difference of at least 3 standard errors in the interim analysis of a major endpoint, which would be the number of patients going into DHF may be needed to justify halting or modifying the study prematurely.

## Procedure for Accounting for Missing, Unused, and Spurious Data.

Missing data will be described, for example, by presenting the number and percentage of individuals in the missing category. All data collected on data collection forms will be used, since only essential data items will be collected. No data will be considered spurious in the analysis since all data will be checked and cleaned before analysis.

## Inclusion in Analysis

All randomised participants, all dosed participants, all eligible participants will be included. If and when a patient is unblinded that patient will not be included in the analysis. Any data from a patient who is lost to follow up will be included until that point.

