## Primary Study Endpoints

Reduction in proportion of individuals who are treated with rupatadine who develop DHF (fluid leakage). In our earlier phase 2 study, we found that approximately 25% of hospitalized patients with dengue infection develop fluid leakage when assessed by serial US Scanning. Therefore, the reduction of the proportion of individuals who develop fluid leakage (DHF) will be assessed. As this trial is conducted in an OPD setting, those who are not admitted will considered to only have DF as any patient who is suspected to develop DHF (fluid leakage) will be admitted. By the time of discharge from hospital, as the patient would have recovered at this time point, if the patient had not developed fluid leakage, he/she will considered as not had DHF.

Evidence of plasma leakage will be considered as:

- detection of free fluid in the abdomen or by the presence of a pleural effusion by USScan
- Or by the presence of a rise in haematocrit of >20% of the baseline.

The haematocrit of the patients will be monitored at least three times a day. If the haematocrit at any given time point is >20% of the patients baseline the patient will be considered as having fluid leakage according to the Sri Lanka National Dengue Management guidelines (15). The patients will also be monitored by daily serial ultrasound scans done by the same person using a portable USScanner in the ward. The scans will be recorded and reassessed by a consultant radiologist to ensure accuracy. Presence of fluid in the pleural and peritoneal cavities or a rise in haematocrit of >20% will be considered as evidence of plasma leakage.

Ultrasound scanning will be done in the supine position to assess the peritoneal fluid: in the hepatorenal angle, subdiaphragmatic position, in paracolic gutters and in the pelvis, and patient will be kept seated upright on the examination bed for 2 minutes for all the pleural fluid to gravitate in to costodiaphragmatic recesses and scanned from the back of the chest hands raised up and crossed back of the head, mid and posterior axillary lines and in seated up position.

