The codes will be kept with the PI and in the event of a SAE or a SAR the codes will be broken. The codes can be accessed all 24 hours. However, since we have already carried out a phase 2 trial to determine the safety of rupatadine 40mg, and was found to be safe, we do not expect any SAE. In addition, rupatadine 40mg has been used in many countries for the treatment of allergic rhinitis and chronic urticaria and SAR or SAE have not been reported.

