# SAFETY REPORTING

## 10.1 Definitions

| Adverse Event (AE) | Any untoward medical occurrence in a participant to whom a medicinal product has been administered, including occurrences which are not necessarily caused by or related to that product. |
| --- | --- |
| Adverse Reaction (AR) | An untoward and unintended response in a participant to an investigational medicinal product which is related to any dose administered to that participant.  The phrase "response to an investigational medicinal product" means that a causal relationship between a trial medication and an AE is at least a reasonable possibility, i.e. the relationship cannot be ruled out.  All cases judged by either the reporting medically qualified professional or the Sponsor as having a reasonable suspected causal relationship to the trial medication qualify as adverse reactions. |
| Serious Adverse Event (SAE) | A serious adverse event is any untoward medical occurrence that:   - results in death - is life-threatening - requires inpatient hospitalisation or prolongation of existing hospitalisation - results in persistent or significant disability/incapacity - consists of a congenital anomaly or birth defect.   Other ‘important medical events’ may also be considered serious if they jeopardise the participant or require an intervention to prevent one of the above consequences.  NOTE: The term "life-threatening" in the definition of "serious" refers to an event in which the participant was at risk of death at the time of the event; it does not refer to an event which hypothetically might have caused death if it were more severe. |
| Serious Adverse Reaction (SAR) | An adverse event that is both serious and, in the opinion of the reporting Investigator, believed with reasonable probability to be due to one of the trial treatments, based on the information provided. |
| Suspected Unexpected Serious Adverse Reaction (SUSAR) | A serious adverse reaction, the nature and severity of which is not consistent with the information about the medicinal product in question set out:   - in the case of a product with a marketing authorisation, in the summary of product characteristics (SmPC) for that product - in the case of any other investigational medicinal product, in the investigator’s brochure (IB) relating to the trial in question. |

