## 10.3 Procedures for Recording Adverse Events

All AEs occurring during the trial / or until the last date of follow up of the last participant, that are observed by the Investigator or reported by the participant, will be recorded on the AER (annexure 4), whether or not attributed to trial medication. All adverse effects will be notified to ERC FMS, USJ and SCCOT of the National Medicinal Regulatory Authority of Sri Lanka as per time frames and guidelines specified by these bodies

The following information will be recorded: description, date of onset and end date, severity, assessment of relatedness to trial medication, other suspect drug or device and action taken. Follow-up information should be provided as necessary.

The severity of events will be assessed on the following scale: 1 = mild, 2 = moderate, 3 = severe. AEs considered related to the trial medication as judged by a medically qualified investigators or the Sponsor will be followed either until resolution, or the event is considered stable.

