# STATISTICS

## Description of Statistical Methods

The interim analysis will be at half way when half the number of patients are recruited. Statistical significance will be calculated for the interim analysis using the

• χ² test for categorical variables in the two groups

• one-way analysis of variance for continuous variables in the two groups

• Kruskal–Wallis for non-parametric continuous variables in the two groups

• Fisher exact test for categorical variables with small sample size in the two groups ( example when the side effects are small in numbers)

• Intention to Treat (ITT) - ITT analysis will be included as this ignores noncompliance, protocol deviations, withdrawal, and anything that happens after randomization

At the end of the trial, the primary endpoint will be the reduction in the number of individuals who develop DHF. And the secondary efficacy endpoints included duration of reduction in stay at hospitals and side effects. Analysis of covariance (ANCOVA) for the primary endpoint and for secondary endpoints will be used as a statistical method in addition to the above basic statistical methods if applicable. This will be supplemented by a repeated measures analysis.

The effect size will also be computed. Standardized mean difference (SMD), which is used for continuous measures such as leakage, and the number needed to treat, which is used for binary outcomes such as side effects in both groups. The SMD will be computed as the difference between drug and placebo divided by their standard deviation:

SMD = (Drug Improvement - Placebo Improvement) / Standard Deviation

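### Dropping unblinded patients makes the analysis set depend on outcome, contradicts intention to treat, and read literally could leave no DHF case in the primary comparison

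*Protocol*

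**What the plan says.** The section Inclusion in Analysis opens by including all randomised, all dosed and all eligible participants. The next sentence reads: "If and when a patient is unblinded that patient will not be included in the analysis".

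Three other rules decide who becomes unblinded and how that relates to the primary endpoint:

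- Section 8.4, on code-breaking: "The codes will be kept with the PI and in the event of a SAE or a SAR the codes will be broken". No condition of relatedness or clinical need is attached.
- Section 10.1 lists among the SAE criteria an untoward occurrence that "requires inpatient hospitalisation or prolongation of existing hospitalisation". Dengue admissions and endpoint events are not exempted, and section 10.3 records adverse events "whether or not attributed to trial medication".
- Primary Study Endpoints: "those who are not admitted will considered to only have DF as any patient who is suspected to develop DHF (fluid leakage) will be admitted". The primary event can therefore be counted only in an admitted patient.

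Two passages point the other way. Description of Statistical Methods, in its list of interim-analysis methods, says: "ITT analysis will be included as this ignores noncompliance, protocol deviations, withdrawal, and anything that happens after randomization". Section 8.7 keeps, for patients withdrawn after prolonged or repeated shock, the data collected up to withdrawal.

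**The concern.** The exclusion is triggered by something that happens after randomisation and is tied to how ill the patient becomes. An analysis set chosen that way no longer compares the groups that randomisation created. The patients most exposed to removal are those with the events that the trial is meant to count.

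An analyst also cannot obey the whole text. Including all randomised patients, ignoring everything after randomisation, and leaving out anyone unblinded are incompatible as soon as one patient is unblinded. The exclusion sentence directly follows the all-randomised sentence and is the more specific of the two, so it would naturally be read as an exception to it.

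**Working it through.** **The chain, read literally**

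1. Suspected DHF leads to admission (Primary Study Endpoints).
2. Admission meets an SAE criterion (section 10.1).
3. An SAE breaks the code (section 8.4).
4. An unblinded patient is not analysed (Inclusion in Analysis).

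Because DHF is counted only in admitted patients, every DHF case passes through all four steps.

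**Inputs**

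- 140 per arm, from the Synopsis. Section 8.4 gives 262 in total and The Number of Participants gives 280 per group.
- 42.8% for placebo and 23.5% for rupatadine, with the arms as in Table 2 of the Background. The Number of Participants attaches the same two figures to the opposite arms. They are ascites proportions alone, in 21 placebo and 17 rupatadine patients recruited early in phase 2, so they are a weak guide to the composite endpoint in outpatients.
- Significance level 0.05, taken as two-sided (assumption).
- Power appears in the text only as 1 − β; 90% is assumed for the check below.

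**The plan's own sample size**

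With mean proportion p̄ = (0.428 + 0.235)/2 = 0.3315:

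n = [1.96·√(2p̄(1−p̄)) + 1.2816·√(p₁(1−p₁) + p₂(1−p₂))]² / (p₁−p₂)²

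= [1.96 × 0.6657 + 1.2816 × 0.6516]² / 0.193² ≈ 123 per arm.

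Allowing for 10% dropout, 123/0.9 gives 137 per arm, or 274 in total. This is close to the Synopsis figure of 140 per arm, 280 in total. One-sided testing at 95% power gives 142 per arm and fits equally well. The point does not depend on which was used.

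**Cases lost in the worst case**

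- Placebo: 140 × 0.428 = 59.9, about 60; 140 − 60 = 80 remain.
- Rupatadine: 140 × 0.235 = 32.9, about 33; 140 − 33 = 107 remain.

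The 80 and 107 are upper limits. Admitted patients without DHF would be dropped by the same route, and the protocol gives no admission rate from which to count them. If the approximately 25% leakage quoted under Primary Study Endpoints is assumed as the placebo rate, 140 × 0.25 = 35 placebo cases would be lost.

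**Partial removal**

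Suppose the same share u of DHF cases is unblinded and removed in each arm. An arm then keeps 140·p·(1−u) cases among 140 − 140·p·u patients. At u = 0.5, placebo keeps 30.0 of 110.0 (27.2%) and rupatadine 16.4 of 123.5 (13.3%). Power by the same method, before dropout:

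| Share removed | Cases, placebo vs rupatadine | Patients left | Power |
|---|---|---|---|
| 0% | 59.9 vs 32.9 | 140 vs 140 | 93% |
| 25% | 44.9 vs 24.7 | 125.0 vs 131.8 | 88% |
| 50% | 30.0 vs 16.4 | 110.0 vs 123.5 | 76% |
| 75% | 15.0 vs 8.2 | 95.1 vs 115.3 | 51% |
| 100% | 0 vs 0 | at most 80 vs 107 | no test possible |

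At 50% the expected difference shrinks from 19.3 to 13.9 percentage points (27.2 − 13.3).

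**The case against.** The strongest reply is that the authors cannot have meant the full chain. Section 8.4 says that no SAE is expected, in a trial whose primary endpoint requires admission. The protocol also plans repeated haematocrits, daily scans and a separate data form for admitted patients, which would be pointless if they were all to be discarded. In phase 2, about a quarter of patients leaked fluid, yet the only SAEs reported are two cases of acute liver failure. Intention to treat and the inclusion of all randomised patients are both stated, and section 8.7 keeps data from patients withdrawn after shock, an event that would plausibly be serious.

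Much of this stands. A reader might infer that the plan definitely deletes every primary event. The documents do not support that, because they contradict themselves and do not settle on deletion. The phase 2 comparison is imperfect, since those patients were already in hospital and admission was not a new event for them. What the reply does not do is remove the exclusion sentence, add an exemption to section 10.1 or limit the trigger in section 8.4.

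A second reply is that only grave SAEs would be unblinded in practice. Endpoint events would still be lost, since liver failure is itself a secondary endpoint. A reader might infer from phase 2 that such losses would fall on the placebo arm. With 2 of 67 on placebo and none reported of 66 on rupatadine (Fisher exact, two-sided p about 0.50), the data are too few to show a difference by arm.

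**Conclusion.** The point holds as a contradiction with a harmful side. The protocol states a rule that removes patients because of post-randomisation events, against its own intention-to-treat and all-randomised statements and out of keeping with section 8.7. Loss of every DHF case is the worst literal reading, probably unintended but not prevented by the text.

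The size depends on how many DHF cases are unblinded, which the documents do not allow one to predict. At 140 per arm and the Table 2 rates, it runs from no loss, through a fall in power from about 93% to 76% when half are removed, to about 60 and 33 cases lost and no comparison possible. These figures rest on small-sample ascites rates, two-sided 5% testing, no dropout and, for the power figures, equal removal shares in the two arms. If the shares differed by arm, the estimate could be biased in either direction.

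This is not a detail left for an analysis plan to fill in. The protocol fixes the rule, and its section on deviations requires ethics committee approval to depart from the statistical plan. It should be corrected before any data are analysed.

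**What to change.** In Inclusion in Analysis, delete the sentence that excludes unblinded patients. State instead that all randomised patients, including any whose code is broken, are analysed in the arm to which they were randomised. An analysis without unblinded patients may be shown as a sensitivity analysis only. This restores the primary comparison whatever is decided about code-breaking.

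Separately, the admission rule under Primary Study Endpoints, the SAE definition in section 10.1 and the code-break trigger in section 8.4 conflict, taken together, with a double-blind design and with the stated expectation of no SAE. The sponsor must reconcile them; no code-break rule is proposed here.

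The cost of the statistical change is one sentence replaced in a protocol amendment, with no added patients, visits or procedures.
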